**Figure 2 F2:**
[figure not shown]
**Reserve-DSD Trial Flow Diagram**.

The two-group experimental design we propose may not completely control for the many variables that can affect DSD. We will control as much as possible for factors we believe are most likely to impact our findings through strict enrollment criteria, and by considering several potential covariates in our analyses: dementia stage, co-morbidities, age, use of CNS-active drugs, pain, infection, dehydration, APOE status, and lifetime complex mental activity including years of formal education, occupation, and past leisure activity.

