### Statistical Analysis

Prior to conducting any statistical analyses, the distributions of all sample data will be examined. Extreme values will be compared with the original data collection forms in order to identify and correct data entry errors. Following this data validation step, sample distributions will be evaluated to determine if they meet the assumptions necessary for use of normal distribution-based statistical methods. If the data are not normally distributed, suitable transformations will be sought to normalize them. Possible transformations include log, square root, and rank transformations. If the data are not sufficiently normalized by transformation, the analysis may proceed using permutation testing to determine significance levels. Categorical variables will be evaluated using models based on the binomial or multinomial distributions. The design of this study is a two-group randomized design within blocks defined by individual nursing homes. Randomization will be conducted at the participant level, so that intervention groups are crossed with nursing homes, rather than nested within them. Repeated measurements will be made within individual participants for up to 30 days. The statistical methods must appropriately account for within-participant correlation among these repeated measurements.

The primary statistical model will be mixed-model analysis of variance (ANOVA). A term representing individual participants will be included as a random effect in the model in order to account for correlated multiple measurements for each participant. Treatment and covariates will be included as fixed effects. The primary outcome variables are delirium severity and duration, and cognitive and physical functioning.

The primary analyses will be based on intent to treat. Thus, participants will be included in the analyses regardless of their level of participation in the treatments or of their loss to follow-up. Participants who have missing data for some time points will not be excluded from analyses. The methodology incorporates all available measurements for each participant into the analysis. Missing values for some observation times will not cause the participant's entire record to be excluded from the analyses, as may occur in usual repeated measures models.

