Potential confounders will be included as covariates in the analysis. If a variable substantially alters either the significance level of a group comparison or a measure of association, that variable will remain in the model in order to control for its confounding effect. Variables that will be evaluated as covariates include those that increase delirium severity and duration, acetylcholinesterase inhibitors, and potential moderators of the association between treatment and outcome.

In order to evaluate differences in change across the study period between the intervention groups, time, and group by time interaction terms will be included in the model. A significant group by time interaction will be of interest, as it would reflect differences in rates of change between the groups. A significant interaction term could yield a non-significant test for the main effect of group, but could reflect an important effect of the intervention. If the test for interaction is significant, the nature of the interaction effect will be evaluated using means plots and post-hoc contrasts.

Hypothesized moderator variables will be evaluated using LISREL and SAS software. Structural models will be specified based on the path diagram presented previously. The path diagram will be used to define the hypothesized structure of the relationships among the variables. Multilevel structural equations modeling (SEM) will be used to evaluate the hypothesized structure, including testing the hypothesized moderator status of the cognitive reserve variables. Tests for moderation are based on regression relationships among the specified variables. These relationships are specified in the SEM model and may be tested based on statistical significance of parameters for direct and indirect effects in the hypothesized model. These relationships can also be tested using sets of mixed-model regression analyses[128-130]. This approach, based on the "Baron and Kenny steps"[128] will be implemented as supplemental analyses using SAS software. Using the regression approach, moderating effects are evaluated as the interaction effect of X and M. Least-squares means with 95% confidence intervals will be used to summarize moderated effects.

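### Covariates stay in the primary model if they move the treatment p-value, so the treatment result helps choose its own test and the error rate is not fixed

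*Protocol article*

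**What the plan says.** The Statistical Analysis section of the protocol article makes a mixed-model ANOVA the primary model. It has a random participant effect, and "Treatment and covariates will be included as fixed effects". The covariates are then chosen by this rule: "If a variable substantially alters either the significance level of a group comparison or a measure of association, that variable will remain" in the model. The stated purpose is "in order to control for its confounding effect".

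The candidates appear in two places. The paragraph after Figure 2 in Methods/Design names "dementia stage, co-morbidities, age, use of CNS-active drugs, pain, infection, dehydration, APOE status, and lifetime complex mental activity". The Statistical Analysis section adds: "Variables that will be evaluated as covariates include those that increase delirium severity and duration, acetylcholinesterase inhibitors, and potential moderators" of the treatment effect. That makes about ten named candidates, and the wording leaves the list open.

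Under Randomization and Control of Cross-Contamination, allocation is by participant, in blocks by nursing home and time. Under Measures of Variables Affecting Vulnerability, dementia stage, age and co-morbidity are obtained at screening or baseline. Pain is recorded daily, and infection, dehydration and CNS-active drugs come from weekly chart reviews.

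**The concern.** In a trial randomised by participant, baseline differences between arms are due to chance, and a valid test already allows for them. Prognostic baseline covariates are worth including for precision, but their effect on this trial's treatment p-value is no ground for choosing them. A rule of that kind selects the model on the result it is meant to test. The nominal p-value and interval are then computed as if the model had been fixed beforehand.

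The rule is also open. It gives no size for a substantial change, no direction and no order of testing. It does not say whether the group comparison in question is the main effect or the group-by-time term. It covers several primary outcomes (delirium duration and severity, the cognitive domains, physical function), and each could end with a different covariate set.

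A second problem lies in the candidates. Pain, infection, dehydration and CNS-active drug use recorded during follow-up could be affected by the intervention. If one of them is, adjusting for it can remove part of the treatment effect. Such a variable moves the estimate and p, so the rule would tend to keep it.

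**Working it through.** The article gives no figure for alpha, power, effect size or explained variance, so there is nothing of the plan's own to reproduce. I checked by simulation how far the error rate depends on the reading of the rule.

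**Inputs from the article.** 256 participants (Abstract); equal allocation, so 256 / 2 = 128 per arm; about 10 candidate covariates.

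**Assumptions.** Two-sided alpha 0.05; no treatment effect; one summary outcome per participant; 10 independent standard normal baseline covariates; joint R² of 0.1, 0.3 or 0.5. Each coefficient is √(R²/10), that is 0.10, 0.17 or 0.22. There are 4,000 simulated trials per setting. The Monte Carlo standard error near 0.05 is √(0.05 × 0.95 / 4000) = 0.0034.

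**Procedure.** Fit the unadjusted model, giving p0 and b0. Add each covariate singly, giving p and b. Keep those that meet the rule, refit, and count final p-values below 0.05.

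| Reading of the rule | R² = 0.1 | R² = 0.3 | R² = 0.5 |
|---|---|---|---|
| No covariates | 0.047 | 0.051 | 0.053 |
| All 10, fixed in advance | 0.052 | 0.052 | 0.052 |
| Keep if p changes by more than 0.05 | 0.049 | 0.056 | 0.047 |
| Keep if p changes more than 1.25-fold, either way | 0.051 | 0.049 | 0.042 |
| Keep if the estimate changes by more than 10% | 0.051 | 0.046 | 0.032 |
| Keep if p crosses 0.05, either way | 0.055 | 0.068 | 0.080 |
| Keep only if p falls by more than 20% | 0.090 | 0.157 | 0.218 |
| Same, stepwise | 0.095 | 0.184 | 0.288 |

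**Power.** At an assumed effect of 0.35 SD, symmetric rules lose roughly 1 to 6 percentage points against the fixed set. A separate simulation used 7 or 12 covariates, each with correlation 0.15 to 0.25, and a 0.3 SD effect. It gave about 90% for fixed adjustment, 87% for a symmetric p-value rule and 80% to 82% for a 10% change-in-estimate rule. Its strongest setting is hard to credit: 12 independent covariates at 0.25 would explain 12 × 0.25² = 75% of the variance. The smaller losses are the safer guide.

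**Group-by-time test.** This was simulated separately with 256 participants, daily measures over 30 days, a random intercept, 10 baseline covariates explaining 30% or 50% of between-person variance, and an intraclass correlation of 0.5 or 0.7 (all assumed). The rule applied was the worst one, keeping a covariate if p falls by at least 20%. With complete data no covariate ever qualified (300 trials per setting). With random dropout from day 7, 95% of single-covariate changes in p were under about 1.09-fold, and about 0.002 or fewer covariates were kept per trial (600 trials per setting). In both cases the rejection rate equalled the unadjusted one.

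**The case against.** The strongest defence is that the text states no direction and names control of confounding as its purpose, so the natural reading is symmetric. On that reading a change threshold does not inflate type I error. This stands. A reader might infer from the rule that the false-positive rate rises several-fold. The article does not support that, because the 9% to 29% figures need a one-directional preference for lower p-values that it nowhere states. They mark the worst case that the wording fails to exclude.

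It also stands that the main simulation uses one outcome per participant. Its figures apply to the group main effect and to delirium duration (one total per participant) and cannot be carried over to the group-by-time test.

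A further defence is that an analysis plan not shown here may supply the threshold. That would not cure the problem, because a threshold still leaves the model chosen on the treatment result. The point concerns a rule the article states, not a detail it leaves out.

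Nor does keeping the statistician blind to treatment coding help. A two-sided p-value is the same when the arm labels are swapped, so the analyst still sees it rise or fall with each covariate.

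Finally, it would go too far to say that every arm difference in a candidate is chance. That holds for baseline values only. For pain, infection, dehydration and drug use recorded later, a difference may be a consequence of treatment, which argues against adjusting for them in the primary model.

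**Conclusion.** The concern holds as a fault in the stated rule, and it should be fixed. The primary model is selected partly on the treatment result, the reported inference ignores this, and the rule's error rate is not fixed. Under the simulation's assumptions, type I error is about 3% to 5.6% for symmetric change thresholds, 5% to 8% if crossing 0.05 triggers retention, and 9% to 29% only under the worst-case reading. A set fixed in advance gives about 5%. Symmetric readings cost some power, an amount that depends on assumed effect sizes and covariate strength. The figures illustrate the range for the group main effect and delirium duration and do not predict this trial's rate. No reading examined improves on a covariate set fixed in advance. The candidates measured after randomisation are a separate reason to change the paragraph; no size can be put on that from the article.

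**What to change.** Delete the retention rule. Before any group comparison is run, even by coded arm, fix one covariate set for the primary treatment model and keep it whatever it does to the p-value:

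- nursing home, as the blocking factor;
- prognostic variables measured at baseline, for example dementia stage, age and Charlson index;
- the baseline value of the outcome where one exists (delirium duration has none), stating whether it enters as a covariate or stays in the response vector.

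Leave post-randomisation values of pain, infection, dehydration and CNS-active drugs out of the primary treatment model. Report the unadjusted result as a sensitivity analysis. Which baseline variables to include is the sponsor's choice; what matters is that the choice is made in advance. The cost is one paragraph of analysis wording and no new data, since the baseline variables are already collected.

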#### Procedure for Implementation

To encourage initial engagement in the activity, the research assistant (RA) will use the System of Least Restrictive Prompts[92] beginning with verbal cueing, followed by verbal cueing and demonstration of the activity. Participants are then encouraged to read out loud, point out facts, work puzzles, ask questions, answer questions, or make choices. RAs will use principles for implementing cognitive activities outlined by Green & Bavelier[93]: active engagement, incremental increases in task difficulty; verbal encouragement and motivation throughout the session; feedback and praise; and variability in tasks. These approaches maximize cognitive processing and restoration.

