#### Scheduling and Duration of Intervention

Participants will receive the intervention for 30 minutes each day for up to 30 consecutive days between the hours of 1 pm and 5 pm. This dosage is based on a consensus report of activity effectiveness compiled by expert recreational therapists from the American Therapeutic Recreation Association and the National Recreation Society[94], standard recreational therapy practice in the nursing home, and studies that have demonstrated the efficacy of daily, 30-minute recreational therapy for behavioral symptoms and functional impairment in persons with dementia[95-97].

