#### Treatment Fidelity

We use several methods to monitor and enhance the reliability of our intervention[98,99]. Intervention RAs are trained in a two-day program that we have developed, standardized, and used for many years to prepare RAs for implementing recreational activities with people who have dementia. These RAs need no special educational background because the activities we use are simple, non-technical games, and exercises. RAs will practice in simulated situations until they achieve 100% agreement on all critical elements of activity intervention before going into the field. The project director (PD) will monitor delivery of the treatment by observing each RA conduct interventions on 10% of sessions in the field (randomly selected). Retraining will be initiated if treatment fidelity is not obtained, as assessed by any "no" answer on the treatment fidelity checklist. Additionally, RAs will complete a treatment fidelity check for any intervention session that was not delivered according to protocol. We will monitor receipt and enactment of treatment using measures for participant adherence to the protocol: intervention dose (time on task and level of participation) and duration (number of treatment days received). Our methods and measures will help us to monitor and ensure the reliability of our intervention, its delivery, receipt and enactment.

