#### Measures of Dosage and Satisfaction with Intervention

Intervention efficacy is often related to dose. During each intervention session, dosage will be obtained by the RA using a stop watch to time the minutes and seconds that the participant engaged in activities (*time on task*: 0 to 30 minutes). The RA also rates the *Level of Participation *using a scale developed by Kovatch and Magliocco for measuring extent of participation in recreational activities (an indicator of cognitive processing)[126]. Scores range from 0 to 3 with descriptors for each numerical rating (dozing, null, passive, active), higher scores indicate greater participation. In our work we achieved interrater reliabilities (ICC) of .99 for time on task and .83 for Level of Participation. Total dosage received will be calculated by weighing each daily time on task score by level of participation score and then summing across intervention days. We will use these data to conduct analyses of the effect of dosage on primary outcomes of the intervention. Activities attempted per cognitive domain are recorded daily.

Because we wish to improve the potential for translating our intervention into practice, we will use investigator-developed *Satisfaction Surveys *to assess staff, family, and participant reports of satisfaction with RESERVE-DSD. These brief surveys are collected at the completion of the 30-day intervention period or at discharge, whichever comes first. We will use these data to refine our intervention for a future effectiveness study.

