One goal of the study is to describe the costs associated with the RESERVE-DSD intervention and developing methods for documenting these costs. This information is important for evaluating the public health impact of the intervention. Because this is a new intervention with little data describing its cost, activity-based costing methods will be used. Determining the cost of the intervention will involve several steps. First, resources used to deliver the intervention will be determined. These resources will include personnel, supplies and other expenses. Next, the amounts used of these resources will be documented. In the case of personnel time, the amount of time spent on activities related to the intervention will be determined using activity diaries for assessment and prescription time, and direct observation by study personnel using the *time on task *measure for the intervention. Finally, the amounts used of each resource will be multiplied by the unit cost of each resource to determine the cost associated with the resource. For personnel costs, the time spent by each provider on activities related to the intervention will be multiplied by the hourly compensation, including benefits, associated with the provider. Finally, costs will be summed across all components of the intervention and divided by the number of patients treated to determine the average cost per patient of delivering the RESERVE-DSD intervention. Because different nursing homes might use different types of personnel for some intervention activities, sensitivity analyses will be used to determine the effect of using different types of personnel on the cost of the intervention. Hence, in addition to the actual average cost of providing the intervention, projected costs based on different types of appropriate personnel providing the intervention will also be constructed. These data will inform a future cost-effectiveness study.

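### Session staff time is costed from time on task, which measures participant engagement, so the session-labour part of the cost per patient is biased downward

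*Protocol article*

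**What the plan says.** The cost paragraph under Statistical Analysis in the Protocol article names two sources of personnel time. Work before the sessions comes from "activity diaries for assessment and prescription time". Delivery of the sessions comes from "direct observation by study personnel using the *time on task *measure for the intervention". The costing rule is then that "the time spent by each provider on activities related to the intervention will be multiplied by the hourly compensation", benefits included. Costs are added over all components and averaged over treated patients.

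Time on task is defined under Measures of Dosage and Satisfaction with Intervention. The research assistant obtains it by "using a stop watch to time the minutes and seconds that the participant engaged in activities", with a range of "0 to 30 minutes". It is weighted by a participation rating and summed over days to give total dose. Treatment Fidelity places it among the measures of participant adherence: "intervention dose (time on task and level of participation) and duration (number of treatment days received".

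**The concern.** The cost formula needs minutes worked by staff. The measure assigned to it records minutes of engagement by the participant. The article fixes this choice explicitly, so it is not a detail left to a fuller document.

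The two quantities can be expected to differ here. Procedure for Implementation describes staff work that precedes engagement: "To encourage initial engagement in the activity, the research assistant (RA) will use the System of Least Restrictive Prompts". The participation scale has levels for dozing and for no participation, and time on task may be zero. A session recorded at zero would be costed at zero, although a research assistant had attended.

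At stake is secondary Aim 3. The article intends the cost data to feed a future cost-effectiveness study, where a unit cost that is too low would make the intervention look more favourable than it is. Staff time that is not logged during the trial may not be recoverable later.

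**Working it through.** The article states no cost, wage, mean time on task or set-up time, so there is no figure of its own to reproduce. The check has two parts: the direction, which follows from the definitions, and an illustration of size, which rests on assumptions.

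**Direction.** Let t be mean time on task per session and L the mean staff time per session. The participant's engagement falls within a session that a research assistant is running, so t ≤ L. The share of session staff time left uncosted is

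u = 1 − t/L ≥ 0,

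with equality only if the participant is engaged for all of the staff time.

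**Inputs for the illustration.**
- Scheduled session and maximum number of sessions, from Scheduling and Duration of Intervention: "Participants will receive the intervention for 30 minutes each day for up to 30 consecutive days". At most 30 × 30/60 = 15.0 hours per participant.
- L = 30 minutes: assumed, meaning that staff are occupied for the whole scheduled slot and for nothing outside it.
- t between 15 and 30 minutes: assumed.

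**Results over 30 sessions.** Hours counted = 30t/60; understatement = 1 − t/30.

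| Assumed t (min) | Hours counted | Staff hours in the slot | Understatement |
|---|---|---|---|
| 15 | 7.5 | 15.0 | 50% |
| 20 | 10.0 | 15.0 | 33% |
| 25 | 12.5 | 15.0 | 17% |
| 27 | 13.5 | 15.0 | 10% |
| 30 | 15.0 | 15.0 | 0% |

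If sessions are cut short when engagement fails, L falls below 30 and the understatement is smaller than shown.

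**From session labour to cost per patient.** If session labour makes up a true share w of the full cost per patient, that cost is understated by w × u. Diary time, supplies and other expenses are costed separately, so w is below 1 and the effect on the reported average is smaller than the table's percentages. The article gives no basis for a value of w.

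**The case against.** The costing rule itself is worded broadly: it covers provider time on activities related to the intervention, and all components are to be summed. One could say that the authors mean staff time and used the name of the dose measure loosely. That reading does not remove the problem. Time on task is a named measure with a single definition in the article, and it is the only source given for session time.

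Several stronger readings are tempting, and the documents do not support them:

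- *Set-up, escort and documentation are costed nowhere.* The broad rule leaves room for them, and an article need not list every logged activity. Adding an assumed 10 to 20 minutes per session would move the understatement to between 1 − 27/40, about 33%, and 1 − 15/50 = 70%, but nothing in the protocol supports those minutes. Some of this work is also specific to the trial. The dedicated area is described under Randomization and Control of Cross-Contamination, and the stopwatch timing, participation ratings and fidelity checks are research data. Charging them could overstate the cost of delivering the intervention in practice.
- *Staff were present for the full 30 minutes regardless.* The Intervention section allows sessions of up to 30 minutes, and under Consent Process assent is sought before each session. No section says that staff stay after a refusal or while a participant dozes.
- *The error is largest in the most impaired.* This is plausible but not stated, and the planned output is one average.
- *The sensitivity analysis repeats the same minutes.* The article says that it varies the type of personnel. It does not say whether minutes stay fixed.

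It also stands that the aim is secondary and descriptive, with no hypothesis or decision rule, and that planned data permit a rough check.

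**Conclusion.** The point holds for session-delivery labour. As written, the plan multiplies a participant measure by a staff wage, and the resulting bias can only run downward. It disappears only under full engagement with no staff work around it.

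The size cannot be derived from the documents. The range of 10% to 50% depends on assumed mean engagement of 27 down to 15 minutes and on a staffed slot of 30 minutes; 0% is possible. A reader might take these percentages as the error in cost per patient. They are not: they apply to session staff time alone.

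Delirium, cognitive, physical-function and moderator analyses are untouched. The point deserves correction because the cost figure is meant for later use and the remedy is inexpensive.

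**What to change.** Have the intervention research assistant log staff start and stop times for each session, covering preparation, prompting, and refused or shortened attempts. In the cost paragraph, name these logged times as the source of session personnel time. Record tasks that exist only for the trial (research ratings, fidelity forms, escort needed only because of the trial area) separately, so that they can be left out of the cost of delivery. Keep time on task solely as the dose measure.

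This costs two extra times on the session form, a line for trial-only tasks and a wording change. The reported cost will probably be somewhat higher.

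If staff times were not logged, the recorded number of treatment days multiplied by the 30 scheduled minutes could serve as an approximate bounding sensitivity analysis beside the estimate from time on task. It would cover the scheduled slot of delivered sessions, but not preparation or refused attempts.
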